### Hypothesis II

Administration of oral NAC at a dose of 900 mg twice a day in combination with second-line during treatment of multidrug resistant tuberculosis (MDR-TB) will protect more than the dose of 900 mg daily against occurrence of serious adverse events without interfering with the effect of second line anti-TB regimen.

### Hypothesis III

Hands-on training, capacity development and setting infrastructure for clinical trials will provide a comprehensive foundation for addressing TB and other infectious diseases of priority in Tanzania.

## Primary objective

To explore the preliminary evidence on the protective effect of NAC through assessing the development of clinical or laboratory-based adverse drug reactions (ADRs) at any frequency during the first six months of local standard of care MDR-TB treatment among patients receiving NAC at a dose of 900 mg daily or 900 mg twice a day compared to those patients treated with the standard of care regimen and placebo.

## Trial pilot and feasibility objectives

To establish the clinical trial unit equipped with standards of operations, clinical trialists, laboratory scientists, and mid-level personnel and create a rapid response infrastructure that will address TB clinical research questions and other infectious diseases in Tanzania.

## Trial design

NAC trial is a phase 2b randomized open labelled superiority trial with three parallel groups and a primary endpoint of occurrence of ADRs at any time during treatment for MDR-TB.

## Methods: participants, interventions, and outcomes

### Study setting

Patients will be recruited at one center, Kibong’oto Infectious Diseases Hospital (KIDH) in Tanzania. The site is experienced in recruitment, hospitalization, safety and efficacy measurement and has the capacity to receive more than 100 MDR-TB patients per year [24]. KIDH has also participated in the International Collaboration for Infectious Diseases Research (ICIDR) consortium to build capacity for MDR-TB trials recruitment and follow-up of a longitudinal cohort of MDR-TB participants through 96 weeks (NCT 03,559,582). In addition, the KIDH research team has demonstrated the capacity of recruiting DS-TB patients for other trials in the Pan African Consortium for Evaluating Anti-TB Antibiotics (PanACEA) with a remarkably high proportion of retention [25].

KIDH is one of the sites determined to set the clinical trial infrastructure for addressing infectious diseases clinical challenges. Currently, the KIDH is developing personnel particularly the clinical trialists, laboratory scientists, and other intermediate staff for conducting clinical trial. The site has demonstrated an initial research capacity through conducting a longitudinal cohort of MDR-TB as a mechanism to prepare for clinical trial [26]. Ongoing research capacity strengthening model at KIDH includes academic training Master or PhD or postdoctoral training, mentoring, collaborations, and networking.

### Eligibility criteria

MDR-TB participants will be eligible, if they are able and willing to provide a written informed consent prior to participation, with age range between 18 and 65 years. They should be newly diagnosed with MDR-TB without a history of using or being on MDR-TB treatment. Decisions on composition of the MDR-TB treatment regimen and timing of initiation will be made by the treating clinicians, but study participants will only be eligible if Karnofsky score of ≥ 50 defined as individuals requiring less considerable or frequent medical care. Female participants should not be pregnant as confirmed by urinary pregnant test to ensure homogeneity of the participants.

Other exclusion criteria include people with previous existing pathology which will preclude testing such as severe baseline hearing loss, central nervous system pathology (i.e., major head trauma, meningitis, encephalitis, or brain metastasis), or untreated mood disorders such as schizophrenia, schizoaffective disorder or psychotic disorder, or using psychotherapeutics like imipramine, and escitalopram. Similarly, participants with known comorbid conditions such as severe liver or renal diseases will be excluded.

### Who will take informed consent?

Recruitment will take place among individuals to KIDH for MDR-TB treatment. Upon identification of a potentially eligible participant, study staff (research nurse or research doctor) will provide information about the study to the participant. As described in greater detail in the study-specific standard operating procedure, the informed consent process will include detailed review of the study informed consent form (ICF) and will allow time to address any questions or concerns each participant may have, and an assessment of each participant’s understanding will be performed before proceeding to the informed consent decision. Illiterate adult patients will have to thumbprint the consent sheet in presence of an impartial witness who will sign the consent sheet in addition. The process will be fully documented and only participants who are able to demonstrate understanding will be asked to provide written informed consent to take part in the study. Written informed consent for study participation must be obtained before any study related procedures are performed. Screening evaluations must be performed within 7 days of entry. Participants screening and enrolment registers will be used to assist with tracking the screening and enrolment process. When informed consent is obtained for the study, a participant identification screening (PID) number will be assigned and eligible participants will receive enrolment PID number. For participants who are found to be ineligible for the study, or who do not enrol in the study for any reason, an electronic case report form (eCRF) will be completed to record the screening outcome.

### Additional consent provisions for collection and use of participant data and biological specimens

Additional consent will be administered for phlebotomy for full pharmacokinetic sampling, which will be performed at 2 weeks after initiation of treatment. The consent will cover week 2 venous blood collection that will be drawn at 1, 2, 6, and 10–12 (late sample per site feasibility) hours and week 8 drawn at 2 and 6 h after medication administration with attempt by single venipuncture for peripheral IV insertion. Such sampling allows for adequate calculation of serum peak (*C*_max_) and estimate total exposure (AUC) of the MDR-TB drugs in the regimen to determine if NAC co-administration unexpectedly impacts these parameters. A maximum of 7 ml will be obtained in heparinized tubes at each draw as up to 4 drugs will be required to be assayed. Additional consent will be obtained for other baseline specimens like stool, urine and saliva for pre-planned future studies.

### Interventions

We will use n-acetylcysteine (NAC) 900 mg in the effervescent tablet preparation as study drug. NAC is manufactured by BioAdventex Pharma Inc., Canada, based on good manufacturing practice standards. One intervention group will receive NAC at a dose of 1800 mg divided twice daily with second line MDR-TB drugs and another intervention group will receive NAC at a dose of 900 mg second line MDR-TB drugs. The control group will receive only second line MDR-TB drugs.

Participants will stop the use of trial medications if there will be any serious adverse events related to the use of NAC for instance allergic reactions or if a participant opts to withdraw from continuing with research participation.

Study nurses will be responsible for observing the participants taking the investigational medicinal product (IMP) during the treatment phase. Study nurses will provide the participants daily IMP and will document administration in the IMP treatment adherence chart. The site trial pharmacist/delegated dispenser will be responsible for dispensing the IMP. Accurate accountability records will be kept by the site to assure that the IMP will not be dispensed to any person who is not a subject under the terms and conditions set forth in this protocol, i.e., delivery to site, inventory at site, use by subject, destruction etc. The investigator/designee will immediately inform the sponsor of any quality issues arising with respect to the IMP. The sponsor will take whatever action is required should such a situation arise. The investigator undertakes to use the IMP only as indicated in this protocol.

### Relevant concomitant care permitted or prohibited during the trial

NAC interacts with nitroglycerin resulting in formation of S-nitroso-NAC, which strongly inhibit platelet aggregation whereas the free sulfhydryl donated from NAC can potentiate the systemic, and coronary vasodilator effects of nitroglycerin in patients with acute myocardial infarction or angina pectoris [27, 28]. This effect increases the risk of hypotension. Likewise, the sulfhydryl NAC modifies the renin-angiotensin II, possibly by inhibition of angiotensin converting enzyme inhibitors, thus reduces conversion of angiotensin I to angiotensin II [29, 30]. Through different mechanisms, NAC modulates glutamate and may results in clinically relevant psychopharmacological properties. In an animal model, Costa-Campos et al. investigated the combination of NAC with antidepressant drugs [31]. Findings show NAC reduced the potency of imipramine and escitalopram but not those of desipramine and bupropion. Conversely, in the same model NAC potentiates fluoxetine. Therefore, participants using imipramine and escitalopram will be excluded while fluoxetine may require dose adjustment.

Although there is no concrete evidence on the interaction of NAC with second line anti-TB drugs for MDR-TB, a number of antimicrobial drugs have the potential to exert central nervous system (CNS) effects and many are associated with stimulant, psychotomimetic and epileptogenic properties [32]. For example, fluoroquinolones can cause CNS effects mediated by gamma-aminobutyric acid (GABA) antagonism, cycloserine and aminoglycosides use can lead to N-Methyl-D-Aspartate (NMDA) agonism, and linezolid and isoniazid can exert monoamine oxidase (MAO) inhibition. In this trial, participants that will be using the psychotomimetic or epileptogenic agents, they will receive second line anti-TB medication without dose adjustment; however, they will be monitored closely according to the protocol.

## Outcomes

### Primary endpoint

The primary outcomes of interests include feasibility metrics related to implementation of sponsor/investigator responsibilities and trial management roles, knowledgeable and skilled trial manager, physician trialists, and laboratory scientists. Evidence generated through this process will guide on the design of the pragmatic trial of NAC in MDR-TB patients.

### Secondary end-point is based on safety and tolerability

Patients will be daily assessed for adverse events including vital signs, physical examinations, routine clinical laboratory tests such as complete metabolic panel, complete blood count, and urinalysis, and interval assessment of electrocardiogram and for those using injectable agents, audiometry testing.Proportion of adverse eventsProportion of adverse events related to experimental treatment

### Secondary endpoints

#### Efficacy

Proportion of MDR-TB patients requiring second-line anti-TB regimen modifications due to ADRsTime for development of AE including the SADRsTB Symptoms profile (Appendix 1)Time to first negative culture on solid/liquid mediaProportion of patients converting to negative sputum culture on solid culture at 4, 6, or 8 months after treatment initiationRate of change of sputum MTB RNA in MBL assay during treatment

#### Pharmacokinetics endpoints of second-line anti-TB drugs

Area under the curve (AUC)Observed *C*_max_ and *T*_max_Volume of distributionElimination half life

### Participant timeline

Screening may be initiated after a written informed consent is obtained. Screening procedures will be performed on multiple days, including on the date of enrolment. For potential participants who do not meet the eligibility criteria, screening may be discontinued once ineligibility is determined. The information will be entered in the case record form to record the screening outcome. Subjects, who following the screening assessments are eligible for the trial and willing to participate, will be randomized/enrolled into the trial and assigned a randomization number. Participant will be followed according to the schedule of events as described in Fig. 1

**Fig. 1 Fig1:**
[figure not shown]
Schedule of events WK denotes week $ The safety parameters includes Hematology: hemoglobin, hematocrit, red blood cell count, white blood cell count with differential, platelet count. Clinical Chemistry: Albumin, urea, creatinine, direct, indirect and total bilirubin, uric acid, total protein, ALP, AST, ALT, gamma‐glutamyl transferase (GGT), lactate dehydrogenase (LDH), phosphate, sodium, potassium, calcium (corrected for albumin), chloride, random/fasting glucose, bicarbonate/CO2

### Sample size

This is a pilot trial to collect information about the effect of NAC that will potentially guide a future larger trial, thus there was no formal power calculation. Therefore, the sample size for the proposed trial will be 20-per arm and thus 60 participants will be enrolled for three arms. However, previously we have found a withdrawal/non-evaluable subject rate from our previous TB clinical trials estimated at 10% [33]. Therefore, a total of 66 MDR-TB patients will be recruited for this clinical trial [34].

### Recruitment

The onsite research coordinators will immediately review newly diagnosed or referred MDR-TB patients and administer processes for potential eligibility and assessment. Likewise, communication with physicians referring patients for MDR-TB treatment from different centres will eventually sensitize potential participants interested to participate to receive referral to KIDH. This will facilitate recruitment.

### Assignment of interventions: allocation

#### Sequence generation

All patients who give consent for participation and those that fulfil the inclusion criteria will be randomized to either the control or the experimental groups in 1:1:1 allocation as per a computer-generated random schedule using permuted blocks of randomization (Fig. 2).

**Fig. 2 Fig2:**
[figure not shown]
All patients who give consent for participation and those that fulfil the inclusion criteria

### Concealment mechanism

This is an open label study. Both the research participants, the investigator team and health care providers will be aware of the assignment. To prevent selection bias by facilitating enrolment of the comparable participants in each arm, allocation concealment will be ensured. Participants will complete all baseline measurements prior to release of the randomization code. A computer-generated randomization numbers will be printed. For every randomization number a code for a treatment will be assigned.

Primary endpoint (ADRs) will be measured by both clinical assessment and laboratory measurements. To avoid ascertainment bias in the measurement of other endpoints such as adverse events, or performance bias in decision to discontinue or modify treatment, or exclusion/attrition bias in the decision to withdraw from the trial or exclude a participant from analysis, blinding will be implemented. Blinding will be at two levels; the trial participants and health care providers. Health care providers include outcomes assessors (physicians and technicians such as aaudiologists), data collectors, laboratory staff, nurses, and pharmacists.

### Implementation

An allocation sequence will be generated by the sponsor representative pharmacist. Site investigators will enroll participants while the site research pharmacist(s) will assign participants to interventions.

### Assignment of interventions

This is an open label thus research participants and the investigator team and health care providers will be aware of the assignment. The later includes clinicians, and data collectors.

### Data collection and management

All case record forms (CRF) both electronic and hard copy pages will be completed for every participant receiving any amount of IMP. Clinical information will be captured in eCRF while laboratory information will be captured in hard copy CRF. For screening failure participants, a screening failure eCRF will be completed. For subjects who are prematurely withdrawn, the visits up to withdrawal plus the withdrawal and follow-up visits need to be completed.

Source documents are defined as all information in original records and certified copies of original records of clinical findings, observations, or other activities in a clinical trial necessary for the reconstruction and evaluation of the trial. Source documents will include, but are not limited to, progress notes, electronic data, screening logs, and recorded data from automated instruments.

All source documents pertaining to this trial will be maintained by the investigators. Source documents will be available for trial-related monitoring, audits, Institutional Review Board (IRB) review and regulatory inspections providing authorized persons direct access to source documents.

### File management at the trial site

It is the responsibility of the investigators to ensure that the trial centre files are maintained in accordance with International Good Clinical Practice Guidelines and the ethical principles that have their origin in the Declaration of Helsinki.

### Records retentions at the trial site

The investigator will retain records and data from the trial for safety reasons and for audit and inspection subsequent to trial completion. The essential documents will be retained according to ICH-GCP guideline. The sponsor will make financial provisions for the investigator to deposit the documents at an external site for safekeeping for as long as required by regulations and the sponsor.

### Plans to promote participant retention and complete follow-up

Although the site has experience with retaining up to 100% of research participants in longitudinal trials, refresher training of research staff will be conducted to maintain the enthusiasm and perseverance of research staff but also, high morale, and compassion to engage and relate with patients. We have found this an important strategy in achieving high retention rates.

### Data management

CRFs will be filled in a timely, accurate and legible manner. Electronic-CRF will be populated in the database while the laboratory CRF entries will be verifiable to source documentation other than the CRF. The CRFs will be filled electronically, in a timely, accurate and legible manner into the Research Electronic Data Capture (REDCap), a highly secured web-based application to capture data for clinical research. CRF entries will be verifiable to source documentation other than the CRF. Site Standard Operating Procedures will be adhered to for all clinical and bioanalytical activities relevant to the quality of the trial. Subject compliance will be monitored throughout the trial. The investigator will be signing and date any test results to verify that the results have been reviewed. The investigator may appoint other sub-investigators to assist with the trial. However, the lead investigator maintain responsibility for the trial and will supervise the sub-investigators. Written IEC/IRB approval will be obtained prior to involvement in the trial. The investigator will ensure that all site personnel are adequately trained in GCP, the protocol, IB, and all trial procedures and requirements.

The study will be monitored to verify that the rights and well-being of human subjects are protected; that trial data are accurate, complete and verifiable with source data; and that the trial is conducted in compliance with the protocol, International GCP, the ethical principles that have their origin in the Declaration of Helsinki and the applicable regulatory requirements.

Monitors assigned by the sponsor will conduct regular site visits for the purpose of monitoring various aspects of the trial. Visits will take place within a predetermined interval, but this may vary during the course of the trial. The investigator and site staff will allow the trial monitor and authorized representatives of the sponsor to inspect all CRFs, written informed consent documents and corresponding source documents (e.g., original medical records), subject records and laboratory raw data, and (2) access clinical supplies, dispensing and storage areas. The investigator and site staff will also assist with monitoring activities if requested and provide adequate time and space for monitoring visits. The monitor will query any missing, confusing, spurious, or otherwise ambiguous data with the investigator. All queries will be resolved in a timely manner. A monitoring log will be maintained recording each visit, the reason for the visit, the monitor’s signature and investigator or designee’s confirmation signature.

### Confidentiality

All site staff, the sponsor, and any sponsor representatives will preserve the confidentiality of all subjects taking part in the trial, in accordance with International GCP, applicable local legislation/regulations. Subject to the requirement for source data verification by the trial personnel by reference to the subject’s notes, confidentiality of all subject identities will be maintained. Only subject trial number and initials will be used on the CRF and in all trial correspondence, as permitted. No material bearing a subject’s name will be kept on file by the sponsor. The written informed consent will contain a clause granting permission for review of the participants’ source data.

## Statistical methods

### Statistical methods for primary and secondary outcomes

The primary efficacy analysis will be conducted using laboratory measurement. Analysis that will be performed includes both Modified Intent to Treat (MITT) defined as analysis of all randomised participants and a Per Protocol (PP) defined as comparison of three arms; control with either 900 mg OD or 900BD or both intervention arms in participants who completed the treatment originally allocated.

The difference in the proportion of patients with ADRs (as defined by the primary efficacy endpoint) between each treatment arm and control arm will be calculated with 95% confidence interval using standard methods**.** In addition, hearing threshold level will be analysed over time using mixed effect models to account for the longitudinal nature of the data. Mean differences between arms in change from baseline (with 95% confidence intervals) will be derived from the fitted model.

The incidence of severe adverse drug reactions as defined by Common Terminology Criteria for Adverse Event (CTCAE) will be calculated in percentage of affected individuals in each arm during the exposure time period of 6 months and the relative risks will be estimated. Time to stable conversion in both phenotypic and molecular (TB molecular bacterial load assay) MTB monitoring methods will be calculated and compared in each arm using adjusted and unadjusted hazard ratio with log-rank test. Furthermore, the rate of patients in each arm converting to negative sputum culture at 4 or 6 or 8 months after treatment initiation will be estimated. Kaplan-Meir estimator will be used to estimate the proportion of patients converting to negative culture and MBLA by specific time.

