No other infectious disease requires treatment strategies of such quantity of drugs, and drug class diversity as MDR-TB, and combined toxicities are not dissimilar to treatment of hematological malignancy. As described elsewhere, the severe adverse drug reactions (ADRs) from medications used to treat MDR-TB include hepatotoxicity, cytopenias, QTc prolongation and cardiac arrhythmia, nephrotoxicity, ototoxicity, peripheral and optic neuropathy, and psychosis [9, 10]. Given the combination of drug-classes, including broad spectrum classes such as the fluoroquinolones, gastrointestinal side effects are common, and can even confuse the presentation of more serious ADRs including hepatoxicity and lactic acidosis [11]. For example, despite the efficacy of bedaquiline, up to 20.8% of people experience bedaquiline related ADRs, with 7.4% serious. ADRs related to bedaquiline were most frequently gastrointestinal (14%), followed by metabolic disorders (8.5%) and nervous system disorders (8.5%) [12]. Likewise, the inclusion of linezolid in MDR-TB regimen has a significant positive effect in improving treatment outcome and reducing mortality, yet the occurrence of ADRs include myelosuppression (33%), neuropathy (30%) whereas other less common ADRs are vomiting, hyperpigmentation and transient visual impairment [13]. Clofazimine is considered safe since the ADRs requiring discontinuation or withdrawal reported have been as low as 0.1% common ADRs are skin discolouration and gastrointestinal side effects with a pooled proportion of 22% [14]. Furthermore, several drugs have overlapping ADRs for instance the fluoroquinolones, bedaquiline, and delamanid all may cause QTc interval prolongation and hepatotoxicity [15].

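### The primary efficacy analysis is tied to laboratory data, while the objective and endpoint count clinical and laboratory ADRs, so the case definition for the main ADR comparison is not settled

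*Protocol article*

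**What the plan says.** Four sections of the protocol article bear on what counts as an event in the ADR comparison.

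- **Primary objective:** "assessing the development of clinical or laboratory-based adverse drug reactions (ADRs) at any frequency during the first six months".
- **Trial design:** "a primary endpoint of occurrence of ADRs at any time during treatment for MDR-TB".
- **Concealment mechanism:** "Primary endpoint (ADRs) will be measured by both clinical assessment and laboratory measurements".
- **Statistical methods for primary and secondary outcomes, first sentence:** "The primary efficacy analysis will be conducted using laboratory measurement". No clinical source is named there.

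The next paragraph of the same statistical section gives the between-arm comparison: "The difference in the proportion of patients with ADRs (as defined by the primary efficacy endpoint) between each treatment arm and control arm", with a 95% confidence interval. No endpoint called the primary efficacy endpoint is defined anywhere in the article.

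A fifth section, Primary endpoint, names something different: "The primary outcomes of interests include feasibility metrics related to implementation of sponsor/investigator responsibilities and trial management roles".

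Under Adverse event reporting and harms, an ADR is an adverse event judged related to drug treatment, whether the investigator observed it or the participant reported it. That definition is not limited to laboratory findings.

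**The concern.** The statistical section gives a narrower data source for the primary efficacy analysis than the objective and endpoint it serves. This is a conflict between statements in the current text, not detail left to an analysis plan.

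The two rules can classify the same patient differently. The article's own list of severe ADRs is "hepatotoxicity, cytopenias, QTc prolongation and cardiac arrhythmia, nephrotoxicity, ototoxicity, peripheral and optic neuropathy, and psychosis". Hepatotoxicity, cytopenias and nephrotoxicity are found by blood or urine tests. Neuropathy and psychosis are found by examination and history. QTc prolongation and hearing loss are found by ECG and audiometry, which the safety and tolerability section lists separately from laboratory tests.

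Two things are at stake. The trial is meant to supply evidence for designing a later one, and the event rate and difference it hands on depend on the case definition. The design is also described as open label, so it is better to have one definition written down before the data are analysed than two that could both be defended afterwards.

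**Working it through.** **The plan's own figure.** The plan gives no figure for this point. The only related one is the sample size: 3 × 20 = 60, and 60 × 1.10 = 66, as stated. The event definition does not enter it, and there is no formal power calculation, so the fix leaves 66 unchanged.

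**The sections side by side.** Test patient: drug-related peripheral neuropathy, all laboratory results normal.

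| Section | What counts | Test patient |
|---|---|---|
| Primary objective | clinical or laboratory ADR | case |
| Trial design | any ADR | case |
| Concealment mechanism | ADRs from clinical and laboratory assessment | case |
| Statistical methods, first sentence | laboratory measurement | event-free on the natural reading |
| Statistical methods, difference in proportions | ADRs under an endpoint not defined by that name | either |
| Primary endpoint | feasibility metrics | not applicable |

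The fifth row is the critical one. If its endpoint is the one in the first three rows, the patient counts. If it takes its meaning from the sentence at the head of its own section, the patient does not. The text does not decide between them.

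**Where clinical ADRs are analysed in any case.**
- Statistical methods: incidence of CTCAE-severe ADRs by arm with relative risks, and a mixed model for hearing threshold.
- Safety and tolerability endpoints: proportion of adverse events, from daily assessment.
- Secondary efficacy endpoints: regimen modification due to ADRs, and time to adverse events.

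**Illustration of how far the two definitions could differ.** Inputs from Background and rationale: linezolid myelosuppression 33% (laboratory), linezolid neuropathy 30% (clinical), clofazimine skin and gastrointestinal reactions 22% (clinical). Assumption: these are per-patient rates in patients taking all the drugs.

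Under independence, P(any ADR) = 1 − Π(1 − pᵢ). The bounds are the largest pᵢ (full overlap) and the sum of the pᵢ (no overlap).

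- Laboratory only: 33%.
- Adding neuropathy: 1 − 0.67 × 0.70 = 53% (range 33% to 63%). Share of cases missed by a laboratory-only count: (0.531 − 0.33) / 0.531 = 38%.
- Adding skin and gastrointestinal reactions: 1 − 0.67 × 0.70 × 0.78 = 63% (range 33% to 85%). Share missed: (0.634 − 0.33) / 0.634 = 48%.
- Bounds on the share missed: 0% with full overlap, and (0.85 − 0.33) / 0.85 = 61% with none.

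**Precision.** With 20 evaluable per arm and equal proportions p, the 95% half-width for a difference is 1.96 × √(2p(1 − p)/20). This is 29 points at p = 0.33, 31 at 0.53 and 30 at 0.63. Under any definition, the direction of a component difference alone says little.

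**The case against.** The strongest reply is that the article never says laboratory measurements *only*. Trial design gives the primary endpoint as any ADR, and Concealment mechanism says it is measured both ways. Read through those two sections, the difference in proportions includes clinical ADRs. This stands in part: exclusion of clinical ADRs is an inference from one sentence and is not stated outright. It does not remove the conflict, because that sentence names one source where another section names two for the same endpoint.

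A second reply is that clinical harm is analysed elsewhere. That also stands. A reader might infer that neuropathy, psychiatric, skin or gastrointestinal ADRs go unreported, and the planned safety, severe-ADR, time-to-event and hearing analyses contradict this. What remains open is whether such events count in the primary ADR comparison.

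A third reply concerns size. The background rates come from separate cohorts and drugs, and no rate is given for hepatotoxicity or nephrotoxicity, so the laboratory share is understated. A reader might also apply the 1.4- to 2.2-fold rise in gastrointestinal intolerance with NAC, quoted in the Discussion, to the 14% bedaquiline gastrointestinal rate. That gives 20% to 31%, an excess of 6 to 17 points that laboratory data would not show. But the ratio comes from studies without MDR-TB patients and the base rate is specific to one drug. Such an excess would also appear in the adverse event proportions. These figures show only that the definition could matter.

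Finally, the trial is exploratory, and the full analysis plan may already settle the definition. That lowers the stakes but does not make the article's own sections agree.

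**Conclusion.** The point holds as an inconsistency in the case definition. Three sections make the objective and endpoint any ADR, from clinical or laboratory assessment. The statistical section ties the primary efficacy analysis to laboratory measurement and refers its between-arm comparison to an endpoint not defined by that name. On the natural reading of its first sentence, clinically detected ADRs do not count in the primary efficacy comparison, though they are reported elsewhere.

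The documents do not support the stronger claim that clinical ADRs are definitely excluded, nor any particular figure for the share missed. The illustrative range of 0% to 61% rests wholly on assumed overlap between rates from different sources. The sample size is unaffected. This should be corrected in the wording before database lock; it does not put the trial's conduct in doubt.

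**What to change.** 1. Correct the first sentence of the statistical section so that the primary ADR comparison uses the endpoint of Primary objective, Trial design and Concealment mechanism: patients with any clinical or laboratory ADR. Replace the undefined term in the next paragraph with that definition and state its time window once, since the objective and the design section word the window differently.
2. Beside that comparison, report the laboratory and clinical components separately by arm, each with the same difference in proportions and 95% confidence interval. State which component ECG and audiometry findings belong to. The reason for the split is that the trial is described as open label and laboratory ADRs are less open to assessor bias.
3. If the sponsor instead intends laboratory ADRs as the primary comparison, reword those three sections to say so and limit the conclusion to laboratory ADRs.
4. In the same edit, reconcile the Primary endpoint section, which names feasibility metrics as the primary outcomes.

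A rule that lets the direction of one component decide the claim is not advised, given half-widths of about 30 points.

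**Cost:** protocol wording and one extra table from data already planned for collection. The headline claim may become narrower if option 3 is chosen.
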